### 4.3 Exclusion criteria

A potential subject who meets any of the following criteria will be excluded from participation in this study:

- Primary diagnosis of: acute cerebral vascular event, acute coronary syndrome, acute pulmonary edema, status asthmaticus, major cardiac arrhythmia, drug overdose, or injury from burn or trauma, diabetic ketoacidosis, hyper-osmolality syndrome, pancreatitis
- Known aortic insufficiency, aortic abnormalities, or intraventricular heart defect, such as ventral septal defect or atrial septal defect
- Known advanced heart failure – meaning NYHA IV functional class HF, on waiting list for heart transplant, LVAD recipient or chronic inotrope use.
- Known end-stage kidney disease (dialysis-dependent CKD stage 5 or  $\text{eGFR} < 15 \text{ mL/min/1.73 m}^2$ )
- Decompensated liver cirrhosis at ED admission (e.g., ascites, hepatic encephalopathy, or variceal bleeding)

- Hemodynamic instability due to active bleeding
- Patient has received >1 liter of IV fluid prior to study randomization
- Requires immediate surgery
- Transfer from another hospital after initiation of therapy (a.o. referred by another hospital ICU) or another in-hospital setting
- Pregnant women
- Trauma patients
- Suspected intra-abdominal hypertension, based on the presence of portal hypertension (i.e. presence of ascites due to liver cirrhosis, esophageal varices or as measured by Doppler ultrasound)
- Inability to obtain IV access
- Patient uncouples from treatment algorithm
- Patient should be excluded based on the opinion of the Clinician/Investigator
- Not able to commence treatment protocol within 1 hour after randomization
- Potential ICU-admission unwanted by advanced care directive (e.g., limited life expectancy)

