## 8.2 Randomisation, blinding and treatment allocation

Subjects will be randomized to either the treatment or control arm of the study, ideally at the moment the treating physician decides to admit the patient to the ED. This randomization process begins as soon as the patient is registered for the ED, even before their arrival.

The randomization process at ED arrival will be facilitated by the REDCap randomization module within REDCap electronic data capture tools hosted at the UMCG. Initially, a researcher will identify potential study participants who meet the inclusion criteria based on information provided by the treating physician. Each prospective participant will be assigned a pseudo-anonymized screening ID generated within the REDCap application. This screening ID will encompass both the deferred consent process and the randomization procedure. The randomization will occur through the REDcap module during the screening, determining the assigned treatment arm.

Once the patient arrives and is included in the study, the assigned treatment arm will be communicated to both the research and treatment teams. Any patients that are enrolled but are found to be ineligible based on exclusion criteria will be exited from the study at that point.

Subjects will be randomized in a 1:1 allocation ratio (treatment to control). It is important to note that the randomization process is not blinded in this study. Both the investigator and the physician are aware of the treatment strategy assigned to each subject.

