#### **8.5 Replacement of individual subjects after withdrawal**

Subjects withdrawn from the study will be replaced by a subsequent patient that presents in the ED matching the inclusion criteria.

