#### **8.6 Follow-up of subjects withdrawn from treatment**

After withdrawal of an individual subject from the study, all data, blood samples collected up to that point will be stored and kept in the database. Upon withdrawal, the subject from the intervention group will receive treatment according to the standard care UMCG-protocol, while the control group will continue with their existing treatment regimen. It is important to note that the measurements for the study will no longer be conducted for the withdrawn subject.

In the event that the participant does not provide consent or withdraws consent, it is up to the participant to indicate whether the data collected up to that point may be retained or must be destroyed.

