## 9. STATISTICAL ANALYSIS

All collected data will be stored in the REDcap, and a complete dataset will be uploaded into R version 1.4.1106 using RStudio (2015, RStudio Team, Boston, MA, United States) for further descriptive and statistical analysis. The main analysis will be conducted based on the intention-to-treat (ITT) principle. Descriptive statistics, such as mean, median, standard deviation, and confidence intervals, will be reported for continuous variables. Categorical variables will be summarized using frequencies and percentages.

The ITT analysis will include all subjects who have signed the deferred consent (DC), met the study eligibility criteria, and were randomized to either the treatment or control arm of the study. The ITT population will be the primary and secondary analysis population for this study.

Depending on the changes in treatment arms and protocol violations, we will conduct both a per protocol (PP) sensitivity analysis and a modified intention-to-treat (mITT) analysis. These analyses will be performed to assess the robustness of the study's findings and account for variations in treatment adherence and protocol deviations.

The per protocol analysis will include only the subjects who strictly adherent to the study protocol, completed the assigned treatment as planned, and did not have any major protocol violations. The mITT analysis will include subjects who met the eligibility criteria, were randomized, and received at least one part of the allocated treatment, such as one fluid bolus based on a fluid responsiveness measurement. Unlike in the ITT analysis, participants who were randomized but did not receive any treatment will be excluded from the mITT analysis.

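### Two events that occur only after randomisation are listed as exclusion criteria, which as written removes those patients from the intention-to-treat set and contradicts the protocol's own description of that set

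*Protocol*

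**What the plan says.** **Protocol 4.3 (Exclusion criteria)** includes three bullets that matter here:
- "Patient uncouples from treatment algorithm"
- "Not able to commence treatment protocol within 1 hour after randomization"
- "Patient should be excluded based on the opinion of the Clinician/Investigator", which carries no time limit.

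**Protocol 8.2 (Randomisation, blinding and treatment allocation)** lets randomisation start before the patient reaches the ED. It states that the trial is open and adds: "Any patients that are enrolled but are found to be ineligible based on exclusion criteria will be exited from the study at that point".

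**Protocol 9 (Statistical analysis)** defines the main set: "The ITT analysis will include all subjects who have signed the deferred consent (DC), met the study eligibility criteria, and were randomized". This set serves both the primary and the secondary analyses. The same section defines a per-protocol set as a sensitivity analysis. It also defines a modified ITT set which, in stated contrast to ITT, leaves out randomised patients who received no treatment.

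**Protocol 4.4 (Sample size calculation)** includes protocol deviations among the causes of the 10% drop-out.

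**Protocol 5.1 (Control)** mandates no therapeutic protocol for the control arm.

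**Protocol 8.3 (Starling SV monitor procedure)** moves patients with a failed device to control treatment and does not name the arm in which they are analysed.

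**Protocol 8.5 and 8.6** deal with withdrawn subjects: "Subjects withdrawn from the study will be replaced by a subsequent patient that presents in the ED matching the inclusion criteria", and "the measurements for the study will no longer be conducted for the withdrawn subject".

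**The concern.** An eligibility criterion should rest on facts that exist before allocation. A patient cannot leave an algorithm before being assigned to it, and the one-hour bullet names randomisation as its starting point. Placed in the exclusion list, both events become conditions of membership in the ITT set.

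Uncoupling can in practice happen only in the guided arm. The trial is open, so the decision to depart from the algorithm is made with the arm known. The primary endpoint is the IV fluid volume over three hours, which is what a clinician changes when departing from a fluid algorithm. If leaving is related to volume and leavers are removed from one arm only, the arms are no longer comparable by randomisation. A difference in mean volume can then arise without any effect of the strategy.

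**Working it through.** **1. The passages side by side**

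| Question | Text that removes the patient | Text that keeps the patient |
|---|---|---|
| Left the algorithm | 4.3 makes it an exclusion; 8.2 exits patients ineligible on exclusion criteria; 9 requires eligibility for ITT | 9 assigns adherence to a separate per-protocol sensitivity analysis |
| Did not start within one hour | Same chain | 9 says ITT, unlike modified ITT, keeps randomised patients who received no treatment |
| Protocol deviation in general | 4.4 counts it as drop-out | 9 runs per-protocol and modified ITT analyses because the ITT set is expected to contain deviations |

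The two columns cannot both apply.

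**2. The plan's own figure**

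Inputs (4.4): means 0.65 and 2.02 L, SDs 2.85 and 3.44 L, two-sided Welch test, alpha 0.05.
- Difference: 2.02 − 0.65 = 1.37 L.
- Average SD: √((2.85² + 3.44²)/2) = 3.159 L.
- Standardised effect: 1.37/3.159 = 0.43.
- Noncentral t with Satterthwaite degrees of freedom: the smallest size for 80% power is 85 per arm (80.25%). The stated 170 is reproduced.
- With all 94 per arm analysed, power on the same inputs is 84.1%.
- The allowance is 188 − 170 = 18 patients, or 9 per arm (9/94 = 9.6%). A 10% removal is therefore used below as an illustration. The allowance covers several causes and both arms, so it does not estimate uncoupling.

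**3. Illustrative size of the bias**

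Assumptions: no true effect, 94 per arm, normal outcome with SD 1, removal from the guided arm only, patients of the same type remaining in control. A fraction f would leave, and they receive k SD more fluid than the others.
- Bias in the guided-minus-control difference = −f × k.
- Standard error = √(2/94) = 0.146 SD.
- Type I error ≈ Φ(−1.96 + |bias|/0.146) + Φ(−1.96 − |bias|/0.146).
- f = 10%, k = 0.5: bias −0.05, ratio 0.343, result 6.4%.
- f = 10%, k = 1: bias −0.10, ratio 0.686, result 10.5%.

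Simulation (20,000 trials, Welch test; k scenarios with leavers replaced):

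| Scenario, guided arm | Bias (SD) | Type I error |
|---|---|---|
| 10% removed, unrelated to volume | 0 | 4.9% |
| 5% removed, k = 0.5 | −0.03 | 5.2% |
| 10% removed, k = 0.5 | −0.05 | 6.1% |
| 10% removed, k = 1 | −0.10 | 10.3% |
| 20% removed, k = 1 | −0.20 | 26% |
| Worst case: exactly the top 10% by volume removed | −0.18 to −0.19 | 28% (29% with replacement) |

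If all randomised patients are kept, type I error stays at 4.7 to 5.2%. If leavers receive less fluid, k is negative and the bias changes sign. For scale, 0.10/0.43 = 23% of the planned standardised effect.

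**The case against.** **The ITT text can be read the other way.** Section 9 says that ITT keeps patients who were never treated, and it plans per-protocol and modified ITT analyses to examine deviations. Section 8.3 keeps device failures in the study as cross-overs. A reader might infer that the main analysis simply becomes a one-sided per-protocol analysis. The text does not support that: it contradicts itself, and nothing says that every deviation is removed. The contradiction stands, because section 9 also requires ITT patients to have "met the study eligibility criteria, and were randomized to either the treatment or control arm".

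**The exit rule may concern baseline facts.** In 8.2 it follows the patient's arrival and inclusion, so it may be meant for ineligibility discovered after pre-arrival randomisation. That is plausible, but the rule refers to the exclusion criteria without limit, and two of them arise later.

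**Leavers are not stated to be unmeasured or replaced.** A reader might infer this from 8.5 and 8.6. Those sections concern withdrawn subjects. Section 8.4 names only the patient's wish and urgent medical reasons, and 8.4.1 gives no specific criteria. The protocol never equates uncoupling or exit with withdrawal, and 8.6 keeps data collected before withdrawal unless the patient asks otherwise. The link is possible in practice but not written.

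**The effect is not wholly one-sided.** A late start can occur in control too, since both arms receive a bolus directly after inclusion (section 3), and the investigator-opinion bullet can act in either arm. Only uncoupling is specific to the guided arm.

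**The direction is not known.** It is tempting to assume that leavers have the highest volumes and the worst course. No passage says so. The rescue rules in 5.1 place extra fluid for several severe conditions inside the algorithm, and a clinician who withholds a bolus from a responder also leaves it, with a lower volume.

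**Conclusion.** The protocol is wrong as written on a point that defines its primary analysis set. Two post-randomisation events are listed as exclusions, and 8.2 and 9 carry them into the ITT definition. Other parts of section 9 say the opposite for untreated patients and leave adherence to another set.

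The contradiction rests on the text alone. The size of the bias does not, because the protocol gives neither a rate of uncoupling nor the volumes that leavers receive. With 10% removed from the guided arm and no true effect, type I error ranges from about 5% (leaving unrelated to volume) through about 6% and 10% (0.5 and 1 SD more fluid) to about 28% in the worst case. The worst case should not be quoted as the expected size. The bias reverses if leavers receive less fluid. No calculation was made for the safety outcomes, so no figure is claimed for them.

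**What to change.** - **4.3:** delete the two post-randomisation bullets and record both events as protocol deviations. Limit the investigator-opinion bullet to facts present before randomisation.
- **8.2:** limit the exit rule in the same way.
- **9:** define ITT as all randomised patients whose data may be used, analysed in the arm allocated whatever their adherence. State that this includes the device-failure cross-overs of 8.3. Leave adherence to the per-protocol analysis.
- **4.4:** remove protocol deviations from the causes of drop-out.
- **8.5 and 8.6:** state that leaving the algorithm is not withdrawal from the study. Continue endpoint collection from the chart unless consent is refused or withdrawn. Limit replacement to patients whose data must be deleted.

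The cost is wording in these sections. No dose or treatment rule changes, and the planned 188 can stay: 94 analysed per arm gives 84.1% power on the protocol's inputs, before any dilution. Non-adherence will dilute the effect somewhat, as an ITT analysis intends.

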#### Groups

Experimental arm: personalized hemodynamic resuscitation (94 patients)

Patients will receive an IV fluid bolus directly after inclusion. Next, measurement of the stroke volume index change in response to the fluid bolus by the Starling SV will be used to determine fluid responsiveness. Vital parameters and fluid responsiveness will be used to guide hemodynamic resuscitation, consisting of IV fluids and/or vasopressors, during the first 3 hours. See chapter 5 and figure 1 for a detailed description of the study procedures.

Control arm: standard care (94 patients)

Patients will receive an IV fluid bolus directly after inclusion. Vital parameters will be used to guide hemodynamic resuscitation, consisting of IV fluids and/or vasopressors, during the first 3 hours. See chapter 5 for a detailed description of the study procedures.

[figure not shown]

**Figure 1: Flowchart personalized protocol.** Adult patients with confirmed or suspected infection with need for hemodynamic resuscitation, will be included into the study. A dynamic assessment of fluid responsiveness using the Starling SV monitor will be performed at every clinical decision point with concordant treatment (volume or vasopressors). MAP: mean arterial pressure; SBP: systolic blood pressure; NE: noradrenaline; PoCUS: Point-of-Care Ultrasound; L: lactate; SI: shock index\*; CI: cardiac index; PLR: passive leg raise; IV: intravenous; \*shock index is heart rate divided by systolic blood pressure;

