#### Control:

Vital parameters, including blood pressure and heart rate, are measured upon ED arrival (triage), immediately after administration of a fluid bolus and at least twice per hour during the first 3 hours. Lactate will be measured at ED arrival (triage) and will be repeated every two hours as long as lactate is > 4 mmol/L. No required therapeutic protocol will be mandated for patient treatment, which will be determined at the discretion of the physician and in accordance with hospital standards.

All fluids administered will be balanced fluids. In addition to the fluid resuscitation as described above, all patients will receive a standard 1.5 L per day of IV fluids from the moment of ED arrival. The total volume of IV fluids will be limited to a maximum of 60 ml/kg over three hours to prevent hypervolemia.

The purpose of the control group is to compare the outcomes of hemodynamic resuscitation guided by the Starling SV monitor in the experimental group with the outcomes of standard care in the control group.

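### Section 4.3 lists two post-randomisation events as exclusion criteria, and section 9 ties ITT membership to eligibility, so the text as written removes randomised patients from the primary analysis

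*Protocol*

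**What the plan says.** Section 4.3 includes two items among the exclusion criteria that describe events after allocation: "Patient uncouples from treatment algorithm" and "Not able to commence treatment protocol within 1 hour after randomization".

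Section 9 states that the main analysis follows the intention-to-treat principle and then defines the set: "The ITT analysis will include all subjects who have signed the deferred consent (DC), met the study eligibility criteria, and were randomized" to either arm. This set serves the primary and secondary analyses. Adherence is dealt with separately, in a per-protocol sensitivity analysis. On the modified ITT set, section 9 adds: "Unlike in the ITT analysis, participants who were randomized but did not receive any treatment will be excluded from the mITT analysis".

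Section 5.1 gives the guided arm a bolus-by-bolus algorithm. For controls it says: "No required therapeutic protocol will be mandated for patient treatment, which will be determined at the discretion of the physician". Section 3 (Groups) uses the same sentence for both arms: "Patients will receive an IV fluid bolus directly after inclusion".

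Section 8.2 says the trial is not blinded and that randomisation may begin before the patient reaches the ED. Section 8.1.1 makes the three-hour IV fluid volume the primary endpoint.

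**The concern.** An exclusion criterion should be a fact that can be established before allocation. A patient can leave an algorithm only after being placed on it, and the one-hour limit runs from randomisation itself. Once such events count as ineligibility, and eligibility decides who is in the ITT set, the primary comparison no longer covers the groups that were randomised.

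The uncoupling item matters most. Controls have no mandated algorithm, so only guided patients can meet it. Whoever applies it knows the arm. The algorithm decides whether each 500 mL bolus is given, so leaving it can change the primary endpoint directly. Removing these patients from one arm can create or hide a difference in volume that the monitor did not cause.

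**Working it through.** **1. Setting the texts side by side**

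| Patient | Section 4.3 with the ITT definition in section 9 | Other text in section 9 |
|---|---|---|
| Guided, starts, then leaves the algorithm | Ineligible, so outside ITT | ITT principle and the separate per-protocol set imply the patient stays |
| Either arm, randomised, never treated | Late-start item met, so outside ITT | The modified-ITT sentence implies the patient stays |
| Either arm, treatment started after more than one hour | Late-start item met, so outside ITT | ITT principle implies the patient stays |

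The modified-ITT sentence speaks only of patients who received no treatment. It does not cover those who started and then uncoupled. Section 4.4 counts protocol deviations within its 10% drop-out allowance, which fits the reading that such patients are lost to the analysis.

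**2. The plan's own sample size**

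Inputs from section 4.4: means 0.65 and 2.02 L, SDs 2.85 and 3.44 L, two-sided Welch test at 0.05. With 85 per arm the power is 80.3% (noncentral t), or 80.0% by simulation with 50,000 replicates. The stated 80% is reproduced. For drop-out, 94 × 0.9 = 84.6, close to the 85 needed.

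**3. Size of the bias in one scenario**

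The protocol gives no three-hour mean or SD, no uncoupling rate and no link between uncoupling and volume, so these are assumptions. Volume is max(0.3, N(1.5, 0.8)) L, with 94 per arm and no true effect. A share u in both arms receives e litres more, and these patients are removed from the guided arm only. The expected spurious reduction is u × e; for u = 10%, 0.10 × 0.5 = 0.05 L and 0.10 × 1.0 = 0.10 L. Type I error is from Welch tests, 4,000 replicates per cell:

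| u | Reduction, e = 0.5 / 1.0 L | Type I error, e = 0.5 / 1.0 L |
|---|---|---|
| 5% | 0.025 / 0.05 L | 5.4% / 7.5% |
| 10% | 0.05 / 0.10 L | 6.8% / 14.2% |
| 20% | 0.10 / 0.20 L | 13.2% / 36.0% |

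A repeat with 10,000 replicates agreed within one percentage point.

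**4. Sensitivity to the assumptions**

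- Half the removed patients higher and half lower in volume: bias about 0, type I error 4.8 to 5.2%.
- All removed patients lower: the bias reverses, by 0.02 to 0.18 L across the six cells.
- A different model, in which removal of 5%, 10% or 20% of the guided arm correlates with volume (20,000 replicates): type I error about 5% at correlation 0; 5.7%, 6.5% and 10.6% at 0.3; 7.0%, 9.9% and 22.0% at 0.5.

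**5. Cost of keeping everyone**

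Use the planning values and assume that a share q of non-adherent guided patients receives control-like volumes. The difference becomes (1 − q) × 1.37 L. With 94 randomised per arm:

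| q | Difference, all kept | Power, all kept | Power, q removed (difference 1.37 L) |
|---|---|---|---|
| 5% | 0.95 × 1.37 = 1.30 L | 80% | 83% |
| 10% | 0.90 × 1.37 = 1.23 L | 75% | 83% |
| 20% | 0.80 × 1.37 = 1.10 L | 64% | 80% |

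The higher power in the last column comes from selection after allocation, so it is no argument for removing patients.

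**The case against.** The strongest reply is that section 9 names the ITT principle, places adherence in the per-protocol set and implies that untreated patients stay in ITT, so a sensible analyst would keep these patients. Section 8.3 also treats device failure as a cross-over and not as an exclusion. This stands in part: removal is the literal result of the definition, not the only reading. It does not clear the text, because the definition and the principle conflict and nothing says which prevails for a patient who started and then uncoupled.

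A reader might infer three stronger things that the documents do not support.

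- *That both items in practice affect only the guided arm.* Controls also have a treatment start, the bolus after inclusion, and randomisation can precede arrival. A late start can therefore occur in either arm. Sensor placement and calibration make a higher guided rate plausible, but no text states one.
- *That non-adherent guided patients are certain to be removed, so that the ITT analysis is really a one-sided per-protocol analysis.* The exit rule in section 8.2, "Any patients that are enrolled but are found to be ineligible based on exclusion criteria will be exited from the study at that point", follows the description of arrival and inclusion. It reads as the eligibility check at that moment and does not show that a patient who uncouples later is exited.
- *That the bias must favour guidance because physicians give fluid the algorithm withheld.* The term for uncoupling is undefined and mentions no physician. Section 5.1 already allows rescue and optional boluses, so some extra fluid is no departure. A departure could also mean a bolus not given, and late starters could receive less within three hours.

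**Conclusion.** The point holds as a defect of wording with consequences for the primary analysis. Two post-randomisation events are listed as exclusion criteria, and the ITT definition carries them into the primary population, against the principle stated in the same section. For uncoupling, the possible selection is confined to the guided arm of an open-label trial whose endpoint is the volume that the algorithm steers. For late start, it is a post-randomisation exclusion in either arm.

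Neither direction nor size can be read from the documents. A spurious reduction of 0.05 to 0.10 L with type I error of about 7 to 14% is one scenario. It rests on an assumed mean of 1.5 L, SD of 0.8 L, 10% removal from the guided arm and 0.5 to 1.0 L more fluid in those removed. With removal unrelated to volume the error stays near 5%, and with lower volumes in those removed the bias reverses. The correction is warranted without settling the size, because the selection is avoidable.

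**What to change.** Delete both items from section 4.3 and record them as protocol deviations, used only to define the per-protocol set. In section 9, define ITT as all randomised patients who met the criteria assessable before randomisation and whose data may be used, analysed in the assigned arm whatever treatment was later started, changed or stopped. State that IV volume continues to be recorded for patients who uncouple or start late. Patients should not be replaced for these reasons under section 8.5, since replacement refills numbers without undoing the selection.

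This is amendment wording and changes no treatment rule. The cost is statistical: non-adherent guided patients dilute the observed difference, and power at 94 per arm may fall to about 80%, 75% or 64% at 5%, 10% or 20% non-adherence under the planning assumptions with control-like volumes. If non-adherence near the upper end is expected, the sample size should allow for it.
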